## Abstract

**Background:**

A four- to seven-fold increase in the prevalence of current mood, anxiety, substance use and any mental disorders in Indigenous adults compared with non-Indigenous Australians has been reported. A lifetime prevalence of major depressive disorder was 23.9%. High rates of comorbid mental disorders indicated a transdiagnostic approach to treatment might be most appropriate. The effectiveness of psychological treatment for Indigenous Australians and adjunct Indigenous spiritual and cultural healing has not previously been evaluated in controlled clinical trials.

**Aims:**

This project aims to develop, deliver and evaluate the effectiveness of an Indigenous model of mental healthcare (IMMHC). Trial registration: ANZCTR Registration Number: ACTRN12618001746224 and World Health Organization Universal Trial Number: U1111-1222-5849.

**Method:**

The IMMHC will be based on transdiagnostic cognitive–behaviour therapy co-designed with the Indigenous community to ensure it is socially and culturally appropriate for Indigenous Australians. The IMMHC will be evaluated in a randomised controlled trial with 110 Indigenous adults diagnosed with a current diagnosis of depression. The primary outcome will be the severity of depression symptoms as determined by changes in Beck Depression Inventory-II score at 6 months post-intervention. Secondary outcomes include anxiety, substance use disorder and quality of life. Outcomes will be assessed at baseline, 6 months post-intervention and 12 months post-intervention.

**Results:**

The study design adheres to the Consolidated Standards of Reporting Trials (CONSORT) statement recommendations and CONSORT extensions for pilot trials. We followed the Standard Protocol Items for Randomised Trials statement recommendations in writing the trial protocol.

**Conclusions:**

This study will likely benefit participants, as well as collaborating Aboriginal Medical Services and health organisations. The transdiagnostic IMMHC has the potential to have a substantial impact on health services delivery in the Indigenous health sector.

The burden of disease attributable to mental health disparities account for as much as 16% in Indigenous Australians^1^ (in this manuscript, we respectfully refer to Aboriginal and Torres Strait Islander people as Indigenous Australians), which may be a major underestimation given accurate data on prevalence of mental disorders in Indigenous Australian have not been available. Our previous mental health prevalence study found that the prevalence of current common mental disorders in a cohort of 544 Indigenous Australians was more than four times that of the general Australian population, markedly higher than previous estimates.^2^ Standardised prevalence rates of current, 12-month and lifetime mood disorders were 16.2% (12.2–20.2%), 19.5% (15.1–23.8%) and 32.2 (27.1–37.3%), respectively; 6.4, 3.1 and 2.2 times higher, respectively, than those of the general Australian population.^3^

Although disproportionate burden of mental disorders among Indigenous people has been attributed to the intergenerational impact of colonisation, others have acknowledged that interventions and services currently available may not be effective or culturally appropriate in supporting the health needs of Indigenous Australians.^4^ Despite this notion, and the high levels of poor mental health,^2^ the efficacy of treatments has rarely been assessed in controlled trials.^5^ An urgent priority exists for the treatment of mental illness, and specifically depression, in this population. Major barriers (cultural, economic and geographic) exist to the utilisation of the limited ambulatory services available. In addition, virtually no robust evidence exists regarding effective and culturally acceptable treatments for mental disorders in Indigenous people.

## Addressing the imbalance

There is now considerable literature available on the importance of culturally appropriate healthcare^6^ and guiding principles need to achieve community acceptance and ‘buy in’ from patients.^7^ Treatments and services that have been efficacious in other health conditions, have been those that include Indigenous people in the design and delivery of the service, and recognise and support cultural concepts of health, social and emotional well-being.^8^ To facilitate an inclusive approach to healthcare development, a desirable methodology is the application of community-based participatory research (CBPR) principles and strategies.^9^ CBPR is a partnership approach to research that equitably involves community members, organisational representatives and researchers in all aspects of the research process and in which all partners contribute expertise and share decision-making and ownership.^9,10^ For instance, some studies have utilised CBPR principles and strategies to establish that land, culture, spirituality, ancestry, family and community are central to the Indigenous Australian understanding of mental health and therefore central to the design of a mental health treatment programme.^11^

For Indigenous Australians, the role of mental health and well-being revolves around holistic concepts of social and emotional well-being. The National Aboriginal and Torres Strait Islander Social Survey (NATSISS).^12^ identifies these concepts including those of cultural attachment/participation, identity, language, spirituality, loss and traditional activities. Dockery^13^ demonstrated the construct validity of the NATSISS through factor analysis. He also found strong scores of association and positive responses to questions investigating levels of happiness and mental health measures derived from the 36-item Short-Form Health Survey. Positive associations of identity and cultural attachment not only associated with happiness, but quantifiable social measures such as education, employment and general health.^13^ Indigenous conceptions of mental health are deeply rooted in the history of colonisation and cultural understandings. Further, the intersection of conceptions of ethnicity and mental illness can be detrimental to the overall social and emotional well-being of a group.^14^ Therefore incorporating social, emotional, spiritual and cultural well-being with psychological therapies is a necessary way forward to reducing the burden of mental health issues for Indigenous Australians. Given that depression is conceptualised within Western epistemology it is argued that there is no ideal measure of depression within Australian Indigenous populations.^15^ Although no specific validation measure is available, nevertheless, the Beck Depression Inventory (BDI) and the BDI-II have been used as a measure of depression in studies with both Australian and Canadian Aboriginal populations.^16^ Moreover, the BDI-II is specifically designed to be used as an outcome measure for cognitive–behaviour therapy (CBT) as it directly assesses the cognitions of the patient.

## Transdiagnostic CBT

Of the psychological therapies, CBT has the strongest evidence base for treating most mental disorders, especially depression, anxiety (including post-traumatic stress disorder) and substance use disorders.^17^ However, CBT could still be further refined to improve outcomes for patients in the treatment of comorbid mental disorders.^17^ Transdiagnostic CBT approaches to treatment that cut across diagnostic boundaries to target the common cognitive, emotional, physiological or interpersonal processes that underlie and maintain mental health symptoms may be most beneficial for individuals with comorbid disorders.^18,19^

A recent meta-analysis of transdiagnostic psychological treatments for adult depressive and anxiety disorders found they resulted in large reductions in anxiety, depression and comorbid depression and anxiety disorders, as well as moderate improvements in quality of life that were maintained for 3–6 months after treatment.^20^ Evidence for transdiagnostic approaches to comorbid substance use and mental disorders is also emerging.^21^ Research, however, is yet to explore the efficacy of either traditional or transdiagnostic CBT among Indigenous populations. A recent qualitative study supported the suitability and effectiveness of CBT for Indigenous peoples.^20^ Five university-educated Aboriginal counsellors, trained in CBT for the project, noted the adaptability of the techniques and reported they were effective in enhancing the well-being of Aboriginal clients.^20^ They also highlighted the need for CBT to be adapted to the social and cultural contexts in which it will be delivered.^20^

## Aims and objectives

The primary objective will be to determine the effectiveness of the model of care (Indigenous model of mental healthcare (IMMHC)) in Indigenous participants with depression by measuring differences between changes in the treatment as usual (TAU) and IMMHC groups on depression scores as measure by the BDI-II from baseline to 6 months.

Secondary objectives will include: evaluating the sustainability of improvements in BDI-II scores over a period of 12 months, monitoring changes in comorbid mental health conditions (any anxiety disorder and/or substance use disorder) over 12 months, and changes in quality of life, changes in subsequent healthcare service use and associated costs, and the effectiveness and appropriateness of recruitment and study procedures over the 12 months.

## Method

### Study design

The study is a randomised controlled trial (RCT) of an IMMHC, based on transdiagnostic CBT and co-designed with the Indigenous community, to evaluate the effectiveness of the treatment of depression. Trial registration: ANZCTR Registration Number: ACTRN12618001746224 and World Health Organization Universal Trial Number: U1111-1222-5849.

The development of the programme will use CBPR principles^22^ and involve community members and Elders; psychologists currently working at the Aboriginal Medical Service (AMS); psychologists from other medical services; Indigenous mental health workers; Indigenous peer-support workers; Indigenous spiritual healers; AMS board members; and current and former patients, and will be manualised upon development. Additional focus groups and one-on-one interviews will be conducted during each phase of the co-design, co-delivery and evaluation of the study. CBPR principles will ensure that a collaborative approach to the research protocol is implemented. This will determine appropriate language and the concepts that are used in the reduction of depression as described by those participating in the CBPR. It will also provide important insight into mental health treatment issues and approaches that need to be considered.

The study design adheres to the Consolidated Standards of Reporting Trials (CONSORT) statement^23^ recommendations and CONSORT extensions for pilot trials.^24^ We followed the Standard Protocol Items for Randomised Trials statement recommendations in writing the trial protocol.^25^

### Randomisation procedure

This will be a randomised controlled parallel group (1:1) trial in adult Indigenous participants with depressive disorders from participating AMSs. Participants will be randomly allocated to IMMHC or TAU (1:1 ratio) in block sizes of 2, 4, 6, 8 and 10. Block sizes will be allocated unequally using Pascal's triangle in the ratio 1:4:6:4:1. This will reduce any predictability of the randomisation codes or the blocks. Concealment will be achieved using opaque envelopes. Those who prepare the randomisation list and/or the concealed envelopes will not be involved in recruitment or data collection.

### Setting

Study activities will be conducted at locations associated with AMSs and other mainstream medical services in Toowoomba and Warwick (South East Queensland, Australia).

### Sample size calculation

The sample size estimates are based on a 2 × 2 repeated measures design comparing changes in BDI-II scores between the two groups (IMMHC and TAU). The primary goal of the study is to compare the change across time in the IMMHC group with the change across time in the TAU group. Sample sizes of 44 in both groups achieve 80% power to detect a difference in mean changes of 6.8 with a standard deviation of 12.8 at the first time point, a standard deviation of 12.0 at the second time point, and a correlation between measurement pairs of 0.6. The significance level (alpha) is a *P*-value of 0.05 using a two-sided, two-sample *t*-test. Based on previous research and experience a 20% drop-out rate is anticipated. Assuming a 20% drop-out rate, the total sample size required is 110.

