### Study arms

#### Intervention – IMMHC

This will be documented and delivered by qualified psychologists trained in the treatment package. The psychologists will receive weekly cultural and clinical supervision and fidelity will be assessed by video-taping a random selection of sessions (*n* = 20) over the duration of the intervention. These tasks will be performed by the supervising clinical psychologist. Competence and fidelity to CBT will be assessed using the Cognitive Therapy Scale – Revised to rate a random selection of videotaped sessions (*n* = 20) over the duration of the entire study. Treatment will consist of both individual and group psychotherapy, as described below. Individual sessions will comprise tailored CBT and traditional spiritual healing; group sessions (co-facilitated with an indigenous health worker) will focus on skills practice, including yarning (informal conversation) about successes and difficulties in application, and developing peer support and reinforcement in this area.

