Individual treatment. The first session will involve the assessment of cognitive and behavioural factors maintaining the disorder. As our previous study^2^ demonstrated that these assessments are typically lengthy, the sessions will be up to 90 min. The treating psychologist will then develop a tailored 6-month treatment plan, in consultation with a senior clinical psychologist and the traditional healer, as well as the participant. Changes in symptomatology may warrant adjustments or changes to the treatment plan. A minimum of 10 and up to 12 sessions of individual treatments will be provided by qualified psychologists using a combination of face-to-face delivery for primary treatment and telephone delivery to facilitate skills practice. The duration of this intervention period will vary for participants, based on their tailored 6-month treatment plan.Group treatment. The efficacy of CBT relies on the use of ‘homework’ or skills practice by the patient to maintain treatment effects. Based on our previous research, we believe that skills practice is likely to be difficult for many Indigenous participants, so we will use traditional healing sessions as a way to do homework. Traditional healers will work with participants to find out what their homework is and practise this with individuals. In addition, follow-up calls by the traditional healers and project team to check on participants and support them between sessions will be incorporated. Group treatment will also be provided via a ‘yarning skills group’ as an adjunct to individual sessions. The purpose of this group is to build on skills learned in individual sessions, provide further peer support in a positive supportive environment, and focus on personal and group strengths. Group treatment aims to be therapeutic, strengths-based, and culturally friendly by: using traditional and spiritual healers, psychologists and Indigenous care co-coordinators as group facilitators; exploring successes in applying skills and learnings obtained from individual sessions; and allowing peers to support each other through learning new behaviours. Consistent with another evidence-based therapy that has adapted CBT for complex presentations using both individual and group CBT; a different psychologist will be used for individual and group sessions. Participants will be offered three to five group sessions over a period of 6 months, with no more than ten participants in each session group.

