#### Quantitative analysis

Intention-to-treat principles will be used for all analyses. Differences in mean change in BDI-II scores from baseline to 6 months between the two groups will be analysed using repeated measures ANOVA, with treatment as the between-subjects factor, and time as within-subjects factor, and an interaction term (time and treatment group). Additional analyses will use mixed models adjusting for baseline covariates including quality of life. We will also calculate the differences between the groups using hierarchical mixed models for continuous variables (BDI-II and BAI scores measured at three time points – baseline, 6 months post-intervention and 12 months post-intervention) containing random intercept and random slope as well as fixed effects for treatment. We will also evaluate changes in diagnostic status using logistic and/or Poisson regression models.

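### The sample size and the primary ANOVA treat IMMHC participants as independent although they share psychologists and therapy groups, so for any positive intraclass correlation the standard error is too small and the 80% power has little slack

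*Protocol article*

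**What the plan says.** Randomisation is by individual, 1:1 (Randomisation procedure).

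Under Intervention – IMMHC, the treatment is "delivered by qualified psychologists trained in the treatment package", in 10 to 12 individual sessions. Three to five group sessions are offered as an adjunct, "with no more than ten participants in each session group". The psychologist who runs the groups is not the one who gives the individual sessions. Peer support is among the aims of the groups. Under TAU, participants see a general practitioner, who may refer them on; the protocol sets up no groups there.

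The Sample size calculation section rests on a two-sided t-test comparing change between the arms. Its claim is: "Sample sizes of 44 in both groups achieve 80% power to detect a difference in mean changes of 6.8". The SDs assumed for BDI-II are 12.8 before and 12.0 after treatment, correlated at 0.6. No ICC or design effect appears.

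Under Quantitative analysis, the primary model is a repeated measures ANOVA with treatment, time and their interaction. Secondary mixed models over three time points are described as "containing random intercept and random slope as well as fixed effects for treatment". The level at which those random effects act is not spelled out.

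**The concern.** People treated by the same psychologist, or in the same small group, tend to have more similar outcomes than people treated separately. Here that similarity is built into one arm only. With two time points, the treatment-by-time interaction in the ANOVA is the two-sample t-test on change, so the planned primary test and the power calculation share the same independence assumption.

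If outcomes are positively correlated within psychologist or group, the mean of the IMMHC arm is less precise than its headcount suggests. The standard error of the treatment difference is then understated, the nominal 5% test rejects too often, and a correct test has less power than stated. This matters because the section on post-study treatment makes adoption of IMMHC as a standard option depend on its proving more efficacious than TAU.

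This is more than detail left to an analysis plan. The power statement and the factors of the primary ANOVA are both fixed in the text, and both conflict with the delivery described in the same document. A later plan could add a cluster term, but that would not make the published power statement allow for clustering.

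**Working it through.** **Inputs from the protocol article.** 44 analysed per arm; difference 6.8; SDs 12.8 and 12.0; correlation 0.6; two-sided alpha 0.05; 20% drop-out; groups of at most ten.

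**Assumed, not in the document.** ICC of the outcome from 0.01 to 0.10; k = 5 clusters of m = 44/5 = 8.8 in the IMMHC arm; no clustering under TAU; total SD unchanged.

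**Step 1: reproduce the plan's figure.**
SD of change = √(12.8² + 12.0² − 2 × 0.6 × 12.8 × 12.0) = √123.52 = 11.11.
SE = 11.11 × √(2/44) = 2.370, and 6.8/2.370 = 2.870.
Power = 81.0% (noncentral t, 86 df) or 81.9% (normal). Total N = 88/0.8 = 110. The stated figures are right under independence.

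**Step 2: cluster the IMMHC arm.**
Design effect DE = 1 + (m − 1) × ICC, in that arm only.
True SE / naive SE = √((1 + DE)/2).
True error of the naive test = 2[1 − Φ(1.96 / ratio)].
True SE = 11.11 × √((DE + 1)/44).
Satterthwaite df = (DE + 1)² / (DE²/(k − 1) + 1/43).

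For ICC 0.05: DE = 1 + 7.8 × 0.05 = 1.39. The ratio is √(2.39/2) = 1.093, so the error is 2[1 − Φ(1.793)] = 7.3%. SE = 11.11 × √(2.39/44) = 2.590, and 6.8/2.590 = 2.625. Power is 73.8% on 86 df. Satterthwaite df = 2.39²/(1.39²/4 + 1/43) = 11.3, which gives 66.9%.

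| ICC (assumed) | DE | SE ratio | True error of naive test | Power, 86 df | Power, Satterthwaite df |
|---|---|---|---|---|---|
| 0.01 | 1.078 | 1.019 | 5.5% | 79.5% | 74% |
| 0.02 | 1.156 | 1.038 | 5.9% | 78.0% | 72% |
| 0.05 | 1.390 | 1.093 | 7.3% | 73.8% | 67% |
| 0.10 | 1.780 | 1.179 | 9.6% | 67.3% | 59% |

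Part of the loss in the last column is the price of few clusters alone: at ICC 0 the same df formula already gives about 76%.

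**Step 3: sensitivity to cluster size (86 df).** For ICC 0.01, 0.02, 0.05 and 0.10:
- groups of 5: 80.2%, 79.5%, 77.2%, 73.6%
- groups of 10: 79.3%, 77.6%, 72.7%, 65.4%

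If the relevant unit were the psychologist and there were only two (22 participants each), ICC 0.05 would give 63.2%. Power falls below 80% once DE exceeds about 1.05, that is at an ICC of about 0.007 with 8.8 per group and about 0.013 with 5 per group.

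**Step 4: baseline adjustment.** Residual SD = 12.0 × √(1 − 0.6²) = 9.6. At ICC 0.05 with five groups, SE = 9.6 × √(2.39/44) = 2.237, and 6.8/2.237 = 3.04. Power is about 79% on the same 11.3 df.

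**Step 5: interval width.** At ICC 0.05 with five groups, the valid change-score interval relative to the naive one is 1.093 × 2.194/1.988 = 1.21, or about 21% wider.

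**The case against.** The strongest reply is that the size of the problem rests on figures the document does not give. That stands. There is no ICC and no number of groups or psychologists. Ten is a ceiling, the group sessions are few and only offered alongside individual treatment, and nothing says group membership is fixed. Psychologist and group need not be nested, because different psychologists run the two formats. With four or five clusters the variance component would also be poorly estimated.

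Some stronger readings are tempting, and the document does not support them:

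- **That the stated power holds only at ICC 0.** It does not. The plan has about one point of slack, so power stays at or above 80% for very small ICCs (Step 3).
- **That every planned model ignores clustering.** The primary ANOVA does. A random intercept and slope over three time points reads as participant level in the secondary models, but the text does not say so, and that detail is commonly left to an analysis plan.
- **That TAU participants are independent.** TAU runs through general practitioners and possible referral in two towns, so some clustering there is possible. What can be said is that the protocol creates none comparable to IMMHC.
- **That baseline adjustment fully restores the power.** A normal approximation gives about 86% at ICC 0.05. With the degrees of freedom that a valid analysis of five clusters needs, it is about 79%.

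None of this removes the point. The direction holds for any positive ICC, and the conflict between delivery and primary analysis is in the text.

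**Conclusion.** The point holds in a conditional form. The arithmetic of the sample size is correct; its independence assumption, shared by the primary ANOVA, does not fit how IMMHC is delivered. For any positive ICC the planned standard error is too small. Over assumed ICCs of 0.01 to 0.10 with five groups of about nine, the nominal 5% test runs at about 5.5% to 9.6%. Power for 6.8 points falls to about 80% to 67% on 86 df, or 74% to 59% with Satterthwaite degrees of freedom. At the low end, or with groups of five, the loss for the naive test is small; with few psychologists carrying large caseloads it would be greater. This is a moderate flaw that can be fixed in the analysis. It should be corrected, and it does not invalidate the trial.

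**What to change.** 1. Record the treating psychologist and the therapy group for each IMMHC participant during delivery, since these may be hard to recover later.
2. Make the 6-month BDI-II analysis partially nested: a random effect in the IMMHC arm for one pre-specified clustering unit (psychologist or therapy group), with the other unit as a sensitivity analysis, and Satterthwaite or Kenward-Roger degrees of freedom.
3. Adjust that analysis for baseline BDI-II, which is already collected.
4. State the level of the random effects in the secondary mixed models.
5. Restate power over an ICC range with the same degrees of freedom. At ICC 0.05 with five groups, this is about 67% for the change-score test and about 79% with baseline adjustment.

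The cost is two identifier fields, revised analysis wording, a less favourable stated power, and a wider interval (about 21% wider at ICC 0.05 with five groups, before baseline adjustment). No extra patients are asked for. The trade-off should be acknowledged: holding 80% power by sample size alone, for the change-score test with groups of ten and ICC 0.05, would take 130 participants instead of 110, even before the loss of degrees of freedom.
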